# Effectiveness and cost-effectiveness of telephone consultations for fever or gastroenteritis using a formalised procedure in general practice: study protocol of a cluster randomised controlled trial

**DOI:** 10.1186/s13063-016-1585-9

**Published:** 2016-09-22

**Keywords:** Telephone consultation, Primary care, Cost-effectiveness, Satisfaction, Compliance, Fever, Gastroenteritis, Cluster randomised controlled trial

## Abstract

**Background:**

Telephone consultations in general practice are on the increase. However, data on their efficiency in terms of out-of-hours general practitioner (GP) workload, visits to hospital emergency departments (ED), cost, patient safety and satisfaction are relatively scant. The aim of this trial is to assess the effectiveness of telephone consultations provided by French emergency call centres in patients presenting with isolated fever or symptoms of gastroenteritis, mainly encountered diseases.

**Methods/design:**

This is a prospective, open-label, multicentre, pragmatic, cluster randomised clinical trial of an estimated 2880 patients making an out-of-hours call to one of six French emergency call centres for assistance with either fever or symptoms of gastroenteritis without seriousness criteria. Each call is handled by a call centre physician. Out-of-hours is 8 p.m. to 7.59 a.m. on weekdays, 1 p.m. to 7.59 a.m. on Saturdays and round-the-clock on Sundays and school holidays. Patients will be enrolled over 1 year.

In the intervention arm, a telephone consultation based on a protocol, the formal Telephone Medical Advice (fTMA), is offered to each patient calling. This protocol aims to overcome a physical consultation during out-of-hours periods. It offers reassurance and explanations, advice on therapeutic management which may include, in addition to hygiene and diet measures, a telephone prescription of antipyretic, analgesic, rehydration medication or others, and recommendations on surveillance of the patient and any action to be taken. The patient is invited to call again if the condition worsens or new symptoms develop and to make an appointment with their family GP during office hours. In the control arm, the call centre physician handles calls as usual. This physician can carry out a telephone consultation with or without a telephone prescription, dispatch an on-duty GP, the fire brigade or an ambulance to the patient, or refer the patient to an on-duty physician or to the ED. Each patient will receive a follow-up call on day 15.

The primary endpoint is the frequency of out-of-hours, face-to-face GP consultations or visits to the ED during the 15 days following the index call. The secondary endpoints measured on day 15 are the number of stays in intensive care, the number of hospital admissions, the number of interventions by the fire brigade, emergency medical and ambulance services, the number and length of prescribed sick-leave episodes, all-cause mortality, morbidity, clinical outcome, patient compliance, patient satisfaction, the number of renewed calls to the call centre, the number of patients receiving multiple face-to-face GP consultations and costs incurred.

**Discussion:**

This trial will assess the effectiveness and the cost-effectiveness of a formalised response to calls for assistance with fever or symptoms of gastroenteritis without seriousness criteria.

**Trial registration:**

ClinicalTrials.gov Identifier: NCT02286245, registered on 9 September 2014.

## Background

Medical advice provided over the telephone is increasingly common in general practice [1–3]. Most calls made to medical call centres concern issues relating to general practice, in particular out-of-hours care. A widespread response to such calls is a telephone consultation [1]. The advice given may relate to action to be taken in the home including surveillance, and may involve telephone prescription and may invite the caller to consult a general practitioner (GP) [4].

Few prospective studies have addressed the effectiveness of advice given over the telephone in primary care in terms of patient compliance, satisfaction and benefit. Moreover, the impact of telephone advice on health costs has not been properly evaluated. A Cochrane review, which identified only five comparative randomised studies on the possibly superior efficacy of telephone consultations over usual care, concluded that such advice had little impact in terms of fewer visits to the family physician or to the hospital emergency department (ED) [1]. The review recommended that high-evidence level studies be conducted with patient satisfaction, safety and cost as endpoints.

In a study in the UK, in which out-of-hours calls to a general practice cooperative were randomised into two groups – namely, telephone consultations with a nurse versus usual general practice care – there was a reduction in costs arising from reduced emergency admissions to hospital in the nurse consultation group [5]. In a study in two urban practices in Scotland, supported by a UK study, telephone consultations for same-day appointments saved general practitioner (GP) time but led to a higher rate of reconsultations in the 2 weeks that followed [6, 7]. On the other hand, the introduction of telephone triage in another UK study significantly reduced by 39 % the demand for face-to-face consultations for patients seeking same-day appointments [8]. The number of ED visits does not seem to be related to telephone consultations [6–9]. The impact on cost seems negligible [7]. In a recent randomised controlled trial conducted in the UK, telephone triage by a nurse or a GP increased the primary care contact compared with usual care for patients calling for a same-day appointment [10, 11]. However, this trial did not focus on out-of-hours periods.

In France, calls for medical emergency are managed by the Service d’Aide Médicale Urgente (SAMU). Calls come from patients with severe symptoms, such as chest main, major trauma, and stroke, and from primary care [12]. In this last subgroup, the most frequently encountered requests for assistance in SAMUs relate to fever and symptoms of gastroenteritis [13, 14]. In response to a call, the medical dispatcher can give medical advice including recommending going into a medical care facility or can send a first aid team (usually the fire brigade), a light ambulance (drivers with first aid training), a GP trained in emergency care or a mobile intensive care unit with an emergency physician. Our study focussed on the management of calls for primary care.

The hypothesis of our study is that the medical advice concluding telephone consultations will provide a benefit to the individual and to society. We postulate that telephone consultations based on a protocol, the formal Telephone Medical Advice (fTMA), might offer an appropriate and effective response to demands made to a call centre. The aim of our study was to determine whether a fTMA can provide a reliable response, in terms of effectiveness and efficiency, in patients presenting with isolated fever or symptoms of gastroenteritis during the out-of-hours period.

## Methods/design

### Design

This is a prospective open-label, multicentre, pragmatic, cluster randomised clinical trial involving six participating centres (SAMU). The centres are randomised into two arms (1:1) according to call management method, either an offer of fTMA (intervention arm) or usual after-hours medical care (control arm). Out-of-hours is 8 p.m. to 7.59 a.m. on weekdays, 1 p.m. to 7.59 a.m. on Saturdays and round-the-clock on Sundays and school holidays. Callers/patients will be randomly selected before inclusion (see Fig. 1 for the study flowchart).

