**Fig. 2 Fig2:**
[figure not shown]
Trial protocol

Reassurance and explanations: addressing nonserious symptoms, the call centre physician provides reassurance to the caller/patient and informs them that home management is possibleTherapeutic management (this may include telephone prescribing [4]): (a) in cases of fever, three hygiene and dietary measures are recommended: removal of the patient’s clothing, airing the room, and offering frequent cool drinks. An antipyretic agent may be prescribed over the telephone if the fever is poorly tolerated. Only one of two drugs should be prescribed, either paracetamol or ibuprofen, the dose depending on the patient’s bodyweight, (b) in cases of symptoms of gastroenteritis, the main measure is early rehydration, i.e. taking small amounts of water at frequent and regular intervals. The call centre physician should explain that this reduces vomiting. An oral rehydration solution (one sachet in 200 mL of water regardless of brand) is recommended in children. The patient should be advised to eat 4 to 6 hours after rehydration. Recommended foods are carrots, rice, apples, bananas, quince, potatoes, and lean meat. Fibres, citrus fruits and cooked fats are to be temporarily avoided. Racecadotril (Tiorfan®), three times a day, can be teleprescribed to decrease bowel movements, the dosage depending on the patient’s body weight. In cases of fever or pain, paracetamol can be prescribed as a function of bodyweightAdvice on surveillance and any action to be taken: the purpose of surveillance is to ensure good tolerance of symptoms. In cases of fever, this is not a return to a normal body temperature. The caller must repeat the advice and medical prescription to the call centre physician to show that they have understood. The patient must make an appointment with their GP during office opening hours. The patient must always call again if the fever persists despite treatment, if their condition worsens, or if further symptoms appear

Patients for whom the call centre physician has to call someone out or refer the patient to a GP on duty or to the ED will be identified and analysed.

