### Outcomes

The primary endpoint is the percentage of patients receiving an out-of-hours, face-to-face consultation with a GP, or who are admitted to hospital, during the 2 weeks following their call to the centre. The motive for the consultation or hospital admission should be the same as the motive initially prompting the call. Secondary endpoints are the following variables measured over the 2 weeks: number of stays in intensive care, number of hospital admissions, number of interventions by the fire brigade, emergency medical and ambulance services, number and length of prescribed sick leave episodes, all-cause mortality, morbidity, clinical outcome, patient compliance, patient satisfaction, number of renewed calls to the call centre, number of patients receiving multiple face-to-face consultations and costs incurred.

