### Sample size

We postulate that fTMA will reduce the percentage of out-of-hours on-duty GP consultations or the number of visits to an ED during the 2 weeks following the index call. In the study by Lattimer et al., the percentage of hospital admissions and ED visits was 12 % after a nurse telephone consultation [17]. In a parallel study, Thompson et al. reported a 21 % versus a 33 % overnight call rate resulting in a home visit by a duty GP in the nurse telephone intervention arm versus the control arm [18]. We estimate that the percentage of out-of-hours consultations and ED visits (our primary endpoint) will be 50 % in the control group. We aim for an absolute reduction of at least 10 % (i.e. from 50 to 40 %) in the intervention arm for each indication (fever/gastroenteritis).

On the assumption of a relatively low weak design effect due to cluster randomisation (about 1.5), and considering a loss of follow-up of 15 %, it is estimated that a sample size of 663 patients/arm/indication will be required for 85 % power and a 5 % alpha risk. If account is taken of an attrition rate of about 8 %, 720 patients will be required (1440/indication, i.e. a total of 2880 patients). This sample size should provide enough power and precision for subgroup analyses (season versus diurnal cycle, weekend versus weekdays).

Inclusions will take place over a full year in order to obtain a representative sample. Each centre will thus include about 240 patients for each indication. A random sample of four patients per week will be drawn outside of an epidemic (about 42 weeks) and of eight patients per week during an epidemic (about 10 weeks) in each centre for each indication. For feasibility reasons, the first patient whose call is closest to the dates and times that will have been randomly drawn for each week of the year of study will be included for each indication.

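### Counting every hour of school holidays as out-of-hours can turn an office-hours visit to the patient's own GP, which the fTMA script asks for, into a primary endpoint event

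*Protocol article*

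**What the plan says.** Out-of-hours is defined in two places of the protocol article, in the Abstract and under Design, with the same content: weekday nights, then "1 p.m. to 7.59 a.m. on Saturdays and round-the-clock on Sundays and school holidays". The part at issue, under Design as in the Abstract, is "round-the-clock on Sundays and school holidays". No other definition is given, and weekday daytime within school holidays is not treated separately.

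Under Outcomes, the primary endpoint is the "percentage of patients receiving an out-of-hours, face-to-face consultation with a GP, or who are admitted to hospital", within two weeks of the call. This wording does not say which GP. Its one filter is that "The motive for the consultation or hospital admission should be the same as the motive initially prompting the call".

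The intervention script (Intervention, Fig. 2) includes: "The patient must make an appointment with their GP during office opening hours". The Abstract also gives this advice for the intervention arm. The description of usual care lists no such instruction.

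The Sample size section is narrower. It postulates that "fTMA will reduce the percentage of out-of-hours on-duty GP consultations". It also says: "Inclusions will take place over a full year in order to obtain a representative sample".

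**The concern.** The definition of out-of-hours decides which GP visits are endpoint events. If every hour of a school-holiday day is out-of-hours, no office hours exist on those days. An fTMA patient who follows the script and sees the family GP on a weekday morning then meets the GP component of the endpoint. The same-motive filter does not remove the visit, because it is a follow-up of the same fever or gastroenteritis.

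That conflicts with the purpose of the intervention, which is to replace a face-to-face contact at night or at the weekend with advice and a later visit in office hours. Adherence to the script would be scored as failure, and only the fTMA arm has that visit as a fixed part of its protocol. At stake is a dilution of the effect that the trial is sized to detect. The same definition also decides which calls are eligible, since Participants admits calls made after hours.

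**Working it through.** **The plan's own figures.** For 50 % versus 40 %, two-sided 5 % alpha and 85 % power, the standard two-proportion formula gives 443 per arm. Then 443 × 1.5 (design effect) = 664.5, against 663 stated, and 664.5 / 0.92 = 722, against 720 stated. The planning rates and the 10-point effect are therefore a sound base. They do not depend on the holiday definition.

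**Model for the literal rule.** The documents give the planned rates of 40 % and 50 %. They do not give the following three quantities, which are assumptions:
- f: share of the year that is school holiday;
- gi: probability, among otherwise event-free fTMA patients, of an office-hours visit to their own GP for the same motive;
- gc: the same probability in control.

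Recorded rate, fTMA = 0.40 + 0.60 × f × gi.

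Recorded rate, control = 0.50 + 0.50 × f × gc.

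Loss of difference = f × (0.60 × gi − 0.50 × gc).

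**Direction.** The difference shrinks whenever 0.60 × gi > 0.50 × gc, that is, unless gc exceeds 1.2 × gi. Equal visit rates already shrink it, because the fTMA arm has more event-free patients (60 % against 50 %) who can be misclassified.

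**Size, school holidays taken literally.** Assume 10 to 16 holiday weeks of 52, gi from 0.20 to 0.40 and gc from 0.10 to 0.20.
- False events, fTMA: 10/52 × 0.60 × 0.20 = 2.3 points, up to 16/52 × 0.60 × 0.40 = 7.4 points.
- False events, control: 10/52 × 0.50 × 0.10 = 1.0 point, up to 16/52 × 0.50 × 0.20 = 3.1 points.
- Smallest net loss (gi = gc = 0.20, 10 weeks): 10/52 × (0.12 − 0.10) = 0.4 point.
- Largest net loss (gi = 0.40, gc = 0.10, 16 weeks): 16/52 × (0.24 − 0.05) = 5.8 points.

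The recorded difference is then 9.6 to 4.2 points. With the plan's effective size of 720 × 0.92 / 1.5 = 442 per arm, power is 85 % without misclassification, 82 % at the small end and 23 % at the large end.

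**Size, if only a few public holidays were meant.** With f = 0.04 and the same visit rates, the loss is 0.04 × 0.02 = 0.1 point to 0.04 × 0.19 = 0.8 point. Even that assumes that GP offices are open on those days, which the documents do not say.

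**Limit of the week count.** Weeks/52 is an approximation. The plan draws four patients per week for about 42 weeks and eight per week for about 10 epidemic weeks, that is 42 × 4 + 10 × 8 = 248 per centre and indication. Ten holiday weeks would hold 40/248 = 16 % of patients if none is epidemic and 80/248 = 32 % if all are, rather than 19 %.

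**The case against.** The strongest reply is that the plan never meant these visits to count. The Sample size section names on-duty GP consultations, and an appointment with one's own GP is not one. The script contrasts office hours with the out-of-hours period throughout. The definition under Design may be there mainly to say which calls are eligible, and a rule for classifying later visits may stand in a document not shown. School holidays may also be a slip for public holidays.

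Much of this stands. It rules out several stronger readings that a reader might infer:
- *That such visits will certainly be counted.* They will if the literal definition is used to classify events. The on-duty wording supports the opposite, and the article does not say which governs.
- *That fTMA-advised appointments in general become events.* Only those on school-holiday days can.
- *That only the fTMA arm is affected.* Control physicians may also advise by telephone, and control patients may see their GP. The bias is a difference between two misclassification rates.
- *That the loss is at least 1.4 points and at most 4.3.* Those values arise if the fTMA visit rate is fixed at twice the control rate. Nothing in the documents supports that ratio. With rates of 30 % in both arms and f = 0.15, the difference is still 9.5 points and power 81 %.

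The reply does not remove the point. The on-duty wording stands in a sample size rationale, while the outcome definition and the Abstract leave the GP unrestricted. This is a disagreement between stated rules, not a detail left to a fuller document. If the word is a slip, it is repeated in both places where the rule is given.

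**Conclusion.** The point holds in conditional form. Read together, the definition of out-of-hours, the script and the outcome definition make a script-compliant weekday visit during school holidays a primary endpoint event, while the Sample size section points the other way. If the literal rule is used, the bias runs against fTMA unless control patients visit their GP in office hours clearly more often (more than 1.2 times the fTMA rate among event-free patients).

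The size cannot be known from the documents. Under the assumed 10 to 16 holiday weeks and visit rates of 20 to 40 % (fTMA) and 10 to 20 % (control), it is about 0.4 to 5.8 of the 10 points. It is below 1 point if a few public holidays were meant and f is about 0.04. The direction is well supported and the size is not. The sponsor should settle the matter before analysis, but it does not show that the trial's result will be wrong.

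**What to change.** Before analysis:
1. State which days are meant and correct the definition in the Abstract and under Design. Check that the corrected definition is also the one used to admit calls.
2. Make the Abstract, Outcomes and Sample size sections agree that the GP component is an out-of-hours consultation with an on-duty GP, so that an office-hours weekday appointment with the patient's own GP never counts.
3. Leave the emergency department/hospital component of the endpoint in place.

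A clock-and-calendar rule combined with the type of GP is preferable to a rule based on each practice's opening hours, because the article does not say that those hours are collected.

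The cost is small. The endpoint derivation is clarified late, after inclusion ended in July 2016 but with follow-up still reported as running, so the change should be dated and recorded as made before analysis. It also depends on the type, date and time of each consultation being recorded. Data collection says that consultations and economic data are captured but does not list these items, so this should be confirmed first.

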**Fig. 1 Fig1:**
[figure not shown]
Flowchart

### Participants

Each call made after hours for either fever (i.e. a body temperature above 38.0 °C) or symptoms of gastroenteritis (nausea and/or vomiting and/or diarrhoea) will be included. The caller has to be over 18 years of age or to be calling regarding a patient aged over 1 year if the caller is not the patient. Fever and gastroenteritic symptoms must have occurred within the previous 72 h.

Exclusion criteria are (1) pregnancy if the caller is the patient, (2) seriousness criteria (i.e. temperature above 41.0 °C, consciousness disorders, skin rash, dyspnoea, signs of dehydration, chest pain, neurological signs, bleeding of the upper or lower gastrointestinal tract and (3) difficulty in communicating (uncommunicative patient, language barrier).

The caller will be informed of the study at the time of their call. Their informed consent will be requested. The caller will receive a copy of the information sheet by mail.

### Intervention

Control arm call centres will handle calls as usual. The call centre physician can carry out a telephone consultation with or without a telephone prescription, dispatch an on-duty GP, the fire brigade or an ambulance to physically examine the patient, or refer the patient to an on-duty physician or to the hospital ED.

The fTMA arm call centres will always offer medical advice over the telephone according to the following protocol (Fig. 2):

**Fig. 2 Fig2:**
[figure not shown]
Trial protocol

Reassurance and explanations: addressing nonserious symptoms, the call centre physician provides reassurance to the caller/patient and informs them that home management is possibleTherapeutic management (this may include telephone prescribing [4]): (a) in cases of fever, three hygiene and dietary measures are recommended: removal of the patient’s clothing, airing the room, and offering frequent cool drinks. An antipyretic agent may be prescribed over the telephone if the fever is poorly tolerated. Only one of two drugs should be prescribed, either paracetamol or ibuprofen, the dose depending on the patient’s bodyweight, (b) in cases of symptoms of gastroenteritis, the main measure is early rehydration, i.e. taking small amounts of water at frequent and regular intervals. The call centre physician should explain that this reduces vomiting. An oral rehydration solution (one sachet in 200 mL of water regardless of brand) is recommended in children. The patient should be advised to eat 4 to 6 hours after rehydration. Recommended foods are carrots, rice, apples, bananas, quince, potatoes, and lean meat. Fibres, citrus fruits and cooked fats are to be temporarily avoided. Racecadotril (Tiorfan®), three times a day, can be teleprescribed to decrease bowel movements, the dosage depending on the patient’s body weight. In cases of fever or pain, paracetamol can be prescribed as a function of bodyweightAdvice on surveillance and any action to be taken: the purpose of surveillance is to ensure good tolerance of symptoms. In cases of fever, this is not a return to a normal body temperature. The caller must repeat the advice and medical prescription to the call centre physician to show that they have understood. The patient must make an appointment with their GP during office opening hours. The patient must always call again if the fever persists despite treatment, if their condition worsens, or if further symptoms appear

Patients for whom the call centre physician has to call someone out or refer the patient to a GP on duty or to the ED will be identified and analysed.

